### Interim analysis

An interim analysis will be performed to evaluate the inclusion rate. At 50% of the planned time for inclusion, the total number of inclusions will be evaluated. If the sample size is less than 47.5% of the target at that time, the duration of steps in the design for the remaining part of the study will be prolonged such that power of 80% is maintained. If the sample size is adjusted at interim analysis, the adjusted dates for cross-over will dictate the allocation of patients to routine practice or best practice for the analysis.

### Safety reporting

No experimental interventions are introduced in this trial. Therefore, no additional safety or health risks are introduced for patients within this trial as compared to regular care and therefore no specific safety monitoring is performed.

### Randomization, blinding and treatment allocation

Randomization is performed after obtaining consent for participation in this trial from the principal investigator and after approval from local (medical ethical) committees of every participating center was obtained. Centers are randomized by an independent statistician using R statistics software to determine the timing of cross-over from current practice to the algorithm [32]. Stratification at randomization is applied for center volume (>45 vs. ≤ 45 pancreatic resections a year, median value based on data from the Dutch Pancreatic Cancer Audit 2014–2015).

Local principal investigators are informed about the allocated time of cross-over of their center, but are blinded to the randomization sequence for all other centers. Blinding of treatment strategy for clinicians or study personnel is not feasible due to the study design. Primary outcomes will be assessed by individual members of an adjudication committee blinded to the intervention (i.e. whether this patient was treated before or after implementation of the algorithm). Patients will be coded by a numeric randomization key, and only the principal investigators have access to this key.

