The expected reduction in the composite primary endpoint was evaluated in two datasets. A relative reduction of 53% was observed in the study on management of pancreatic fistula (i.e. 34% after primary catheter drainage versus 73% after primary relaparotomy). Using the Dutch Pancreatic Cancer Audit data, centers were divided into four quartiles based on the incidence of the primary endpoint after pancreatoduodenectomy. The incidence was 21% in the worst-scoring quartile containing 292 patients from four centers. The incidence of the composite primary endpoint was 8% (i.e. relative reduction 62%) in the best-scoring quartile containing 331 patients who underwent pancreatoduodenectomy in five centers. Based on these outcomes, a relative reduction of 50% in the primary endpoint was used for the sample size in the PORSCH trial. This was the minimal reduction deemed clinically relevant by the members of the trial steering committee and stakeholders from the Dutch Pancreatic Cancer Group.

The required sample size was calculated using the formula for stepped-wedge designs using an expected incidence of 13.8%, a relative reduction of 50%, two-sided alpha of 0.05 and power of 0.80 [30]. The intra-cluster correlation (ICC) estimated from the Dutch Pancreatic Cancer Audit was 0.009 (95% CI 0.006–0.049). As the within-period and between-period ICC were the same, the cluster autocorrelation was set at 1 [31]. Table 3 provides the required sample size for different numbers of participating sites (i.e. clusters). This number dictates the inclusion time in this study design, which was based on the total number of pancreatoduodenectomies performed in the last 2 years according to the Dutch Pancreatic Cancer Audit. As each cluster will contain one of the 17 participating centers, the number of sequences is equal to the number of clusters. Based on the annual number of pancreatoduodenectomies performed in The Netherlands in 2014 and 2015, the planned study duration is 92 weeks to include the required sample size of 1186 pancreatoduodenectomies with complete enumeration (i.e. 5.1 weeks per step for 18 time periods). The total duration of the trial will be 96 weeks, including a 4-week wash-in period.

**Table 3 Tab3:** Required sample size for different numbers of participating centers

Number of centers	Cluster size^**a**^	Required sample size	Expected inclusions	Inclusion time^**b**^
14	5.9	1239	1239	28
15	5.1	1220	1224	25
16	4.5	1204	1224	24
17	3.9	1186	1193	22

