^a^ Average number of patients per center for every step in the stepped-wedge design

^b^ Inclusion time in months including 4 weeks wash-in phase

As we include patients undergoing all types of pancreatic resection in this trial, the total number of patients registered in this trial is expected to be 25% more than the required sample size. We will perform the primary analyses in patients undergoing pancreatoduodenectomy and subsequently in all patients undergoing any type of pancreatic resection.

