The primary endpoint (i.e. composite of post-pancreatectomy bleeding, new-onset organ failure and death) is a binary variable that will be analyzed using mixed-effects logistic regression analysis. Secondary endpoints will be analyzed using crude and adjusted mixed-effects logistic regression analysis (for binary outcomes) or mixed-effects linear regression analysis (for continuous outcomes). Crude analysis will include a random intercept and random slope at the level of the hospital to adjust for the design, and no other covariates. Adjusted analysis will additionally include the following covariates: calendar time and time since cross-over as a continuous variable, predictors for postoperative pancreatic fistula (i.e. soft pancreatic texture, small-diameter pancreatic duct, increasing blood loss during pancreatic resection and underlying disease that is *not* pancreatitis or pancreatic adenocarcinoma [33]) and predictors for the primary endpoint (i.e. male gender, increasing age, American Society of Anesthesiologists (ASA) classification > 2, index pancreatic resection pancreatoduodenectomy; based on multivariable logistic regression analysis as presented in Table 4). Relevant model assumptions (such as distribution of residuals) will be checked for all models; if deviations from the analysis plan are required this will be described. Crude and adjusted odds ratios with 95% confidence interval and *p* value will be reported.

**Table 4 Tab4:** Factors associated with the composite primary endpoint in 1686 patients undergoing pancreatic resection in the Dutch Pancreatic Cancer Audit

Outcome	Univariable		Multivariable	
	OR (95% CI)	*P* value	OR (95% CI)	*P* value
Male gender	1.64 (1.20–2.23)	0.002	1.64 (1.19–2.27)	0.002
Age	1.02 (1.01–1.04)	0.003	1.02 (1.00–1.03)	0.04
BMI	1.00 (1.00–1.01)	0.52		
ECOG performance score		0.17		
2 vs. 1	1.29 (0.92–1.79)	0.14		
3 vs. 1	1.59 (0.95–2.66)	0.08		
4 vs. 1	0.44 (0.06–3.33)	0.43		
ASA classification (3 and 4 vs. 1 and 2)	1.87 (1.33–2.61)	< 0.001	1.79 (1.26–2.53)	0.001
Preoperative additional nutrition		0.05		
Oral vs. none	0.98 (0.70–1.38)	0.91		
Via nasogastric tube vs. none	1.74 (0.92–3.28)	0.90		
Via TPN vs. none	4.04 (1.17–14.02)	0.03		
Preoperative biliary drainage	0.97 (0.71–1.32)	0.82		
Distal pancreatectomy vs. pancreatoduodenectomy	0.50 (0.31–0.79)	0.003	0.58 (0.36–0.94)	0.03
Texture pancreas (hard/firm vs. soft/normal)	1.22 (0.86–1.73)	0.26		

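### The cross-over order is stratified by center volume, but volume is in neither covariate list; adding it is a minor improvement, not a correction of an invalid analysis

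*Protocol article*

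**What the plan says.** Under Randomization, blinding and treatment allocation, centers are randomized to the timing of their cross-over. "Stratification at randomization is applied for center volume", the two strata being more than 45 and at most 45 pancreatic resections a year.

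Under Statistical analysis, the primary endpoint is to be analyzed by mixed-effects logistic regression. The crude model has a hospital-level random intercept and random slope and no covariates. For the other model, "Adjusted analysis will additionally include the following covariates: calendar time and time since cross-over as a continuous variable", followed by named predictors of fistula and of the composite endpoint. The list is specific, and center volume is not on it.

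Under Subgroup and sensitivity analyses, the same cut at 45 resections a year defines a subgroup analysis. That is the only analytical use of volume.

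**The concern.** A factor used to stratify randomization is by convention carried into the analysis model. Here it is known for every center and needs no new data, yet it is left out without comment.

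Precision could be affected. Once time is in a stepped-wedge model, the effect estimate combines within-center contrasts with contrasts between centers that have and have not yet crossed over. The between-hospital variance therefore contributes to the standard error. A random intercept represents that variance but does not explain it; a center-level covariate can explain part of it.

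The article gives indirect reason to think volume might matter. The Discussion says early signs of leakage are often missed in centers that see few fistulas. The Sample size calculation section reports 21% against 8% for the composite in the worst and best center quartiles. Neither is a direct estimate of a volume effect.

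**Working it through.** **Inputs from the Sample size calculation section**

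- "expected incidence of 13.8%, a relative reduction of 50%, two-sided alpha of 0.05 and power of 0.80", so 13.8% against 6.9%, a difference of 0.069.
- Intra-cluster correlation (ICC) 0.009, interval 0.006 to 0.049; "the cluster autocorrelation was set at 1".
- 17 centers, one per sequence, and "5.1 weeks per step for 18 time periods".
- 3.9 patients per center per step (Table 3).

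**Assumptions, not in the documents**

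- Share of between-hospital variance explained by volume: 0, 10, 25 or 50%.
- Eight high-volume centers with 5.4 patients per period and nine low-volume centers with 2.57, averaging about 3.9.
- Cross-over orders in which the two strata are balanced over the steps.

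**Step 1: reproduce the plan's figure.** Two proportions, 13.8% against 6.9%, pooled variance, no continuity correction: 305 per arm, 610 in total. The stepped-wedge design effect, with k = 17 steps, n = 3.9, r = 0.009 and one measurement at baseline and per step, is

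[1 + r(kn + n − 1)] / [1 + r(kn/2 + n − 1)] × 3(1 − r) / [2(k − 1/k)]

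= 1.6228 / 1.3245 × 0.0877 = 0.1075.

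N = 610 × 0.1075 × 18 periods ≈ 1180, against the stated "required sample size of 1186 pancreatoduodenectomies with complete enumeration". The agreement is within 1%, so the inputs are read correctly.

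**Step 2: fit volume and compare standard errors.** Generalized least squares on the risk-difference scale, random hospital intercept, ICC 0.009. Power = Φ(0.069/SE − 1.96). Without volume and with period effects, SE is 0.0246 and power is Φ(2.80 − 1.96) = 80.0%. With volume fitted as a fixed effect:

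| Variance explained by volume | SE ratio, period effects | Power, period effects | SE ratio, no time term | Power, no time term |
|---|---|---|---|---|
| 0% | 1.001 | 80.0% | 1.0005 | 95.8% |
| 10% | 0.994 | 80.4% | 0.996 | 96.0% |
| 25% | 0.982 | 81.3% | 0.990 | 96.2% |
| 50% | 0.960 | 83.1% | 0.977 | 96.6% |

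Without volume, power in the model with no time term is 95.8%. Linear calendar time gives the same SE ratios as period effects to within 0.0005. A random slope with half the intercept variance does not enlarge the gain (SE ratio 0.966 at 50% explained). Over the stated ICC interval, the largest SE reduction is 4.6%, at ICC 0.049 with 50% explained, where power goes from 69.4% to 73.5%.

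**Step 3: logistic check.** Random-intercept logistic models with calendar time were simulated, 300 runs per scenario. The empirical SE of the log odds ratio, without and with volume, was 0.256 and 0.256 (0% explained), 0.283 and 0.284 (25%), and 0.260 and 0.259 (50%). The model-based SE did fall, for example from 0.265 to 0.257 at 50%, but the actual spread of the estimates hardly moved. Under no effect, rejection rates were 3 to 6% with or without volume, in models with and without time.

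**The case against.** The strongest objection is that nothing is shown to be wrong. The randomized unit is the center, and the center is in the model. Volume is a fixed attribute of that unit, every center contributes control and intervention periods, and the random intercept already absorbs most of any volume difference. The documents give no rate by volume, and Table 4 does not list it, so the size of any gain is conjecture. The logistic simulation shows no material gain even at 50% explained. With 17 centers, another center-level term has a price. A separate analysis plan may also deal with the point.

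Most of this stands. Three stronger readings are tempting, and the documents support none of them:

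- **That the planned standard error is too large, or that precision is there for the taking.** This holds only if volume explains between-hospital variance. If it explains none, adding it costs a trace of precision.
- **That the analysis departs from the randomization in a way that threatens validity.** No bias or inflation of type I error appears. The departure is one of form.
- **That permutation must respect the strata.** No randomization test is planned, so the question does not arise.

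It is also not certain which list governs the primary model. The crude and adjusted versions are introduced in the sentence on secondary endpoints, whereas the primary endpoint is assigned only to mixed-effects logistic regression. Volume is absent under either reading.

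The objection does not remove the omission itself. The article states a specific covariate list, and the one factor the design stratified on is missing. That Table 4 omits volume does not show that volume is unimportant.

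**Conclusion.** The point holds as a minor improvement. The cross-over order is stratified by a factor that both stated models leave out. At ICC 0.009, including it would change the standard error by between +0.1% and about −4%: 0 to about 3 points of power with period effects, under 1 point without a time term. These figures rest on an assumed 0 to 50% of between-hospital variance explained by volume, on assumed center sizes, and on a linear approximation. The logistic simulation, limited to 300 runs per scenario and a random intercept, suggests that the real gain lies toward the low end. Type I error control and freedom from bias are not in question.

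**What to change.** Add center volume (more than 45 against at most 45 resections a year) as a fixed effect to the mixed models for the primary endpoint, at least to the adjusted model that includes calendar time. If it is deliberately left out, say so and give the reason. Settle this before outcome data are compared, so that no choice between models with and without volume remains open.

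The cost is one line in the Statistical analysis section and one between-hospital degree of freedom among 17 centers. No new data are needed, since the variable was already used for randomization and is planned for the subgroup analysis.

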### Statistical analysis

For statistical analysis, outcomes of all patients undergoing pancreatic resection before implementation of the algorithm (i.e. current practice) will be compared to outcomes of all patients undergoing pancreatic resection after implementation of the algorithm (i.e. best practice). The date of pancreatic resection will determine the study phase in which a patient will be analyzed. The primary analysis will be on an intention-to-treat basis according to the planned date of cross-over to care according to the algorithm. Data from patients in the wash-in period will be excluded from the primary analysis. Secondary analyses include a per-protocol analysis in which we will compare patients who receive care according to the algorithm (i.e. all resections after first implementation presentation at a center, including patients undergoing pancreatic resection in the wash-in period) to patients undergoing pancreatic resection before cross-over. When appropriate, 95% confidence intervals will be calculated. In all analyses a two-sided value of alpha of 0.05 will be used to denote statistical significance.

Missing baseline data will be imputed using multiple imputation techniques. The primary analysis will be performed using the multiple imputed data. A complete case analysis will be performed to check for inconsistencies. Baseline data will be analyzed and reported using standard descriptive statistics. The chi-square or Fisher’s exact test is used to compare categorical variables as appropriate. Parametric continuous variables are presented as mean with standard deviation (SD) and are compared using Student’s *t* test. Non-parametric continuous variables are presented as median with interquartile range (IQR) and are compared using the Mann-Whitney *U* test.

The primary endpoint (i.e. composite of post-pancreatectomy bleeding, new-onset organ failure and death) is a binary variable that will be analyzed using mixed-effects logistic regression analysis. Secondary endpoints will be analyzed using crude and adjusted mixed-effects logistic regression analysis (for binary outcomes) or mixed-effects linear regression analysis (for continuous outcomes). Crude analysis will include a random intercept and random slope at the level of the hospital to adjust for the design, and no other covariates. Adjusted analysis will additionally include the following covariates: calendar time and time since cross-over as a continuous variable, predictors for postoperative pancreatic fistula (i.e. soft pancreatic texture, small-diameter pancreatic duct, increasing blood loss during pancreatic resection and underlying disease that is *not* pancreatitis or pancreatic adenocarcinoma [33]) and predictors for the primary endpoint (i.e. male gender, increasing age, American Society of Anesthesiologists (ASA) classification > 2, index pancreatic resection pancreatoduodenectomy; based on multivariable logistic regression analysis as presented in Table 4). Relevant model assumptions (such as distribution of residuals) will be checked for all models; if deviations from the analysis plan are required this will be described. Crude and adjusted odds ratios with 95% confidence interval and *p* value will be reported.

**Table 4 Tab4:** Factors associated with the composite primary endpoint in 1686 patients undergoing pancreatic resection in the Dutch Pancreatic Cancer Audit

Outcome	Univariable		Multivariable	
	OR (95% CI)	*P* value	OR (95% CI)	*P* value
Male gender	1.64 (1.20–2.23)	0.002	1.64 (1.19–2.27)	0.002
Age	1.02 (1.01–1.04)	0.003	1.02 (1.00–1.03)	0.04
BMI	1.00 (1.00–1.01)	0.52		
ECOG performance score		0.17		
2 vs. 1	1.29 (0.92–1.79)	0.14		
3 vs. 1	1.59 (0.95–2.66)	0.08		
4 vs. 1	0.44 (0.06–3.33)	0.43		
ASA classification (3 and 4 vs. 1 and 2)	1.87 (1.33–2.61)	< 0.001	1.79 (1.26–2.53)	0.001
Preoperative additional nutrition		0.05		
Oral vs. none	0.98 (0.70–1.38)	0.91		
Via nasogastric tube vs. none	1.74 (0.92–3.28)	0.90		
Via TPN vs. none	4.04 (1.17–14.02)	0.03		
Preoperative biliary drainage	0.97 (0.71–1.32)	0.82		
Distal pancreatectomy vs. pancreatoduodenectomy	0.50 (0.31–0.79)	0.003	0.58 (0.36–0.94)	0.03
Texture pancreas (hard/firm vs. soft/normal)	1.22 (0.86–1.73)	0.26		

Data from the Dutch Pancreatic Cancer Audit (2014–2015). Presented are the outcomes of univariable and multivariable logistic regression model showing gender, age, American Society of Anesthesiologists (ASA) classification and type of index resection are independently associated with the occurrence of the composite primary endpoint

*OR* odds ratio, *BMI* body mass index, *ECOG* Eastern Cooperative Oncology Group, *TPN* total parental nutrition

Length of hospital stay will be calculated from the date of the index pancreatic resection and will be analyzed using mixed-effects Cox proportional hazards regression, using discharge alive as the outcome event. Patients who die during the index hospitalization will be censored at the day of death. Length of ICU stay and time to resolution of pancreatic fistula (i.e. time to removal of the last abdominal drain or completion of pancreatectomy) will be analyzed using a zero-inflated negative binominal regression model.

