In general, in-hospital mortality after pancreatoduodenectomy varies widely among Dutch centers (interquartile range 0–8%). This variability appears to be explained by differences in failure-to-rescue rates between centers (i.e. mortality in patients with major postoperative complications) [11]. A recent multicenter propensity-score-matched study by the Dutch Pancreatic Cancer Group identified doubling of mortality after primary relaparotomy, as compared with primary minimally invasive catheter drainage for postoperative pancreatic fistula (36% vs. 14%, *P* = 0.007; risk ratio 0.39; 95% confidence interval 0.20–0.75) [9]. Relaparotomy causes a major inflammatory response syndrome in patients who are already ill, which might induce or aggravate multiple organ failure and possibly death [12]. As an alternative to relaparotomy, minimally invasive percutaneous catheter drainage has been shown to be very effective in the majority of patients [9]. In daily practice, however, both treatment strategies are still frequently performed (primary catheter drainage 73%, primary relaparotomy 27%) with no change towards a more minimally invasive management strategy [9]. This might be related to the lack of (international) guidelines on postoperative patient monitoring and management of complications.

This trial is designed to investigate whether implementation of an algorithm for postoperative care focusing on early detection and minimally invasive step-up management of postoperative pancreatic fistula results in a lower rate of major complications and death after pancreatic resection, as compared with current practice. This trial will also evaluate the superiority of the algorithm in other clinical outcomes, the number of patients receiving chemotherapy, quality of life, healthcare resource utilization and costs.

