Secondary endpoints include individual components of the composite endpoint and an adapted version of the primary endpoint in which only complications are included that are deemed by the blinded adjudication committee to be directly related to a pancreatic fistula. Other secondary endpoints are: the Comprehensive Complication Index (CCI) [25] based on complications grade 3 or higher according to the Clavien-Dindo classification [19], postoperative pancreatic fistula [21], gastroenterostomy leakage, postoperative bile leakage [22], delayed gastric emptying [23], chyle leakage [26], new-onset acute pancreatitis [24], number and timing of abdominal CT scans, number, timing and type of invasive (re-)interventions, admission to the Intensive Care Unit (ICU), length of ICU stay, length of hospital stay, readmission rate, number of patients receiving adjuvant chemotherapy at 90 day follow up, duration of postoperative pancreatic fistula (time to removal of the last abdominal drain or completion of pancreatectomy), success of implementation (i.e. based on number and timing of abdominal CT scans and proportion of patients’ days in which the algorithm was not followed). Daily data on the incidence and duration of SIRS, sepsis and organ failure (according to the definitions in Table 1 and according to Sequential Organ Failure Assessment (SOFA) and the Multiple Organ Dysfunction Score (MODS)) are also collected [27–29]. In addition, we aim to evaluate the impact on quality of life, total direct and indirect costs and budget impact (see “Economic evaluation”).

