### Subgroup and sensitivity analyses

Analyses will be performed both on the group of patients undergoing pancreatoduodenectomy and on the entire group of all patients undergoing pancreatic resection. Additional subgroup analyses will be performed based on adherence to the study protocol (i.e. proportion of patients’ days in which the algorithm is followed), hospital volume (> 45 vs. ≤ 45 pancreatic resections a year), pathologic nature of disease (malignant disease), in patients with postoperative pancreatic fistula and in patients with a high risk of pancreatic fistula [34].

A sensitivity analysis will be performed to evaluate the impact on outcomes related to postoperative pancreatic fistula. To this aim, the adjudication will be asked if an outcome was related to postoperative pancreatic fistula and if this outcome could have been prevented by adherence to the algorithm. Two separate analyses will be performed on the Comprehensive Complication Index: one analysis including all complications and one adjusted analysis, in which interventions imposed by the algorithm (e.g. minimal invasive catheter drainage and use of antibiotic management for abdominal sepsis) will not be included in the calculation. A sensitivity analysis will be performed to evaluate the success of implementation. Centers will be divided into equally sized clusters based on the percentage of additional abdominal CT scans per patient after implementation, as compared with before implementation. Separate analysis will be performed for each group.

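### One two-sided 0.05 rule covers every analysis and superiority is also sought on other outcomes, but the 17 to 18 secondary outcomes and the subgroups have no order, gate, adjustment or exploratory label

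*Protocol article*

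**What the plan says.** All of this is in the protocol article.

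- **Aim (Background).** "This trial will also evaluate the superiority of the algorithm in other clinical outcomes". The same sentence goes on to chemotherapy receipt, quality of life, resource use and costs.
- **Decision rule (Statistical analysis).** "In all analyses a two-sided value of alpha of 0.05 will be used to denote statistical significance". No analysis is exempted.
- **Secondary outcomes (Outcomes).** "Secondary endpoints include individual components of the composite endpoint and an adapted version of the primary endpoint". The list then continues: "Other secondary endpoints are: the Comprehensive Complication Index (CCI) [25] based on complications grade 3 or higher according to the Clavien-Dindo classification", followed by a long run of further outcomes.
- **Models and reporting (Statistical analysis).** "Secondary endpoints will be analyzed using crude and adjusted mixed-effects logistic regression analysis" for binary outcomes, with linear models for continuous ones. Then: "Crude and adjusted odds ratios with 95% confidence interval and *p* value will be reported".
- **Populations (Sample size calculation).** "We will perform the primary analyses in patients undergoing pancreatoduodenectomy and subsequently in all patients undergoing any type of pancreatic resection".
- **Subgroups (Subgroup and sensitivity analyses).** Five factors are named: adherence, "hospital volume (> 45 vs. ≤ 45 pancreatic resections a year), pathologic nature of disease (malignant disease"), presence of a postoperative fistula, and high fistula risk.

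The article names one composite primary endpoint and bases the sample size on it alone. It gives no testing order among the secondary outcomes, no condition tying them to the primary result, no multiplicity adjustment and no statement that secondary or subgroup results are exploratory.

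**The concern.** Multiplicity is often left to a statistical analysis plan, and silence on it here would be no finding. This article is not silent. It states a significance rule for every analysis and, separately, an aim of superiority on outcomes other than the primary. Read together, they leave any secondary or subgroup p value below 0.05 open to being reported as significant, and a favourable one as evidence of superiority, whatever the primary analysis shows.

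The trial is meant to inform nationwide practice. If the primary result were neutral, the published text would not prevent a single favourable secondary outcome or subgroup from carrying the conclusion, with no control over how often that happens by chance. A later analysis plan that added an order or an exploratory label would have to depart from the published rule.

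**Working it through.** **1. The plan's own figure.** Required sample size for 17 centers: 1186.

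Inputs (Sample size calculation and Table 3): incidence 13.8%, halved to 6.9%; two-sided alpha 0.05; power 0.80; ICC 0.009; 17 steps; 3.9 patients per center per step.

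- Two-proportion formula: 305 per arm, 610 in total.
- Stepped-wedge design effect: [1 + 0.009(17 × 3.9 + 3.9 − 1)] / [1 + 0.009(½ × 17 × 3.9 + 3.9 − 1)] × 3(1 − 0.009) / [2(17 − 1/17)] = (1.6228 / 1.3245) × (2.973 / 33.882) = 0.1075.
- Total over 18 periods: 610 × 0.1075 × 18 ≈ 1180. A Hussey-Hughes variance solved for 80% power gives 1183.

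The stated 1186 is reproduced with the whole 0.05 spent on the one primary endpoint. The secondary tests do not enter this calculation.

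**2. Counting the secondary family (Outcomes section).** Bleeding, organ failure, death and the fistula-related composite (4); Comprehensive Complication Index (5); pancreatic fistula (6); gastroenterostomy leakage (7); bile leakage (8); delayed gastric emptying (9); chyle leakage (10); acute pancreatitis (11); ICU admission (12); ICU stay (13); hospital stay (14); readmission (15); adjuvant chemotherapy (16); fistula duration (17). Counting re-interventions as one more outcome gives 18. CT use, implementation measures, SIRS, sepsis, SOFA, MODS, quality of life and costs are left out.

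**3. Chance findings if the algorithm has no effect.** Each test is taken to be valid at two-sided 0.05, so 0.025 in the favourable direction. The article gives no correlations between outcomes. I assume a common correlation ρ between the test statistics and show a range.

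- At least one favourable: 1 − ∫ φ(u) · Φ[(1.96 − √ρ·u)/√(1 − ρ)]^k du
- At least one in either direction: 1 − ∫ φ(u) · {Φ[(1.96 − √ρ·u)/√(1 − ρ)] − Φ[(−1.96 − √ρ·u)/√(1 − ρ)]}^k du
- At ρ = 0 with k = 18 these reduce to 1 − 0.975^18 = 0.366 and 1 − 0.95^18 = 0.603.

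| Tests | Direction | ρ = 0 | ρ = 0.3 | ρ = 0.5 | ρ = 0.7 |
|---|---|---|---|---|---|
| k = 18 | favourable | 0.37 | 0.26 | 0.20 | 0.14 |
| k = 18 | either | 0.60 | 0.51 | 0.40 | 0.28 |
| k = 17 | favourable | 0.35 | 0.25 | 0.19 | 0.14 |

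Against 0.025 for one favourable result, the k = 18 row is 0.14/0.025 ≈ 6 to 0.37/0.025 ≈ 15 times as large, and 8 times at ρ = 0.5.

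**4. Adding subgroups.** Six extra tests (five factors, with both volume strata tested) make k = 24. The favourable chance becomes 0.46, 0.31, 0.23 and 0.16 at the same four correlations. The count of six is an assumption, because the article does not say how subgroups will be tested.

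**The case against.** The best defence has four parts.

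- **The article is a condensed protocol.** A testing order could sit in a plan that is not shown. This would answer a complaint of omission. It does not answer a stated rule that covers every analysis.
- **The article already has a structure.** There is one primary endpoint, the sample size rests on it, the pancreatoduodenectomy population comes first, and the rest is labelled secondary, subgroup or sensitivity. This stands. What is missing is any order among the secondary outcomes and any statement of what a significant one may support.
- **The family can be inflated.** This also stands. Quality of life belongs with the economic evaluation, which states no significance test for it. SIRS, sepsis, SOFA and MODS data are only said to be collected. Hospital stay, ICU stay and fistula duration have their own models, with no stated crude and adjusted pair. Several outcomes overlap, which points away from the ρ = 0 end of the range.
- **The article never says that any p value below 0.05 becomes a superiority claim.** True. That reading joins the Background aim to the significance rule, and nothing in the text blocks it.

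Two stronger readings are tempting. A reader might infer that a chance superiority claim is likely. The 0.28 to 0.60 range also counts results favouring current practice; for results favouring the algorithm the figure is 0.14 to 0.37, so it is substantial but below one half. A reader might also infer that subgroups will often look discordant because each level is tested separately. The article does not describe testing within levels and does not exclude interaction tests, so no discordance rate can be derived from it.

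**Conclusion.** The point holds as a rule that is fixed badly, limited to secondary and subgroup claims. Under no effect, the chance of at least one nominally significant secondary outcome favouring the algorithm is about 0.20, with a range of 0.14 to 0.37. In either direction it is about 0.40, with a range of 0.28 to 0.60. These figures rest on 18 outcomes (17 changes little), one valid test per outcome, and an assumed common correlation between 0 and 0.7.

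It should not be read as a fault in the primary inference. The primary endpoint keeps its 5% error, and the required 1186 is reproduced without reference to the secondary tests. The change is still worth making, because it alters what the trial may claim.

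**What to change.** Change the wording in three places.

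1. **Statistical analysis.** Limit the two-sided 0.05 rule to the single primary analysis. State that all secondary and subgroup results are exploratory, reported as estimates with 95% confidence intervals and without claims of significance or superiority. If the sponsor wants confirmatory secondary claims, keep a short prespecified set under multiplicity control. One example is the three components of the composite, tested only if the primary analysis is significant, with Holm's procedure (smallest p value compared with 0.05/3 = 0.0167). This is one scheme among several; the exploratory label alone is enough.
2. **Subgroup and sensitivity analyses.** For subgroups fixed before surgery or by center volume, report the treatment-by-subgroup interaction with the estimate in every level.
3. **Background.** For outcomes outside any confirmatory set, replace the superiority aim with an aim of exploring the effect.

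This needs no extra patients, data or procedures. The price is that secondary outcomes can no longer be presented as proven superiority, and any retained confirmatory set faces a stricter threshold.
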